### Tissue analysis

2.6.

Resected specimens will be analyzed using established immunohistochemical protocols [14,38]. FFPE sections will be stained to quantify TAM density (Iba1), vascular features (CD31, fibrinogen), and Schwann cell markers (CD56). Ferumoxytol deposition within resected tissue will be assessed using Perls’ Prussian blue staining for iron and immunolabelling of the dextran ferumoxytol coating (Dx1). The cellular localization of ferumoxytol uptake will be further characterized using dual immunohistochemistry and immunofluorescence. Laser ablation inductively coupled plasma mass spectrometry (LA-ICP-MS) will also be used to detect and spatially map iron derived from USPIO uptake within resected tumor tissue [39–41]. To evaluate in detail the phenotype and spatial distribution of TAMs in each tumor and their relationship to USPIO uptake, selected tissue specimens will be analyzed using imaging mass cytometry and a previously validated antibody panel [11,42].

### Sample size and tumor groups

2.7.

The planned number of participants is 39 (12 sporadic VS, 12 NF2-VS patients, 15 glioma patients). This sample size reflects feasibility and the expected recruitment capacity of a single-center pilot study requiring serial advanced MRI over three days, ferumoxytol infusion, and, in surgical participants, tissue acquisition for imaging-histology comparison. Although glioma and VS are biologically distinct, both are characterized by macrophage-rich inflammatory tumor microenvironments that are implicated in tumor growth, progression and treatment response. The inclusion of both intra-axial gliomas and extra-axial VS permits assessment of our hypotheses across two clinically important CNS tumor settings with differing characteristics.

This pilot study will allow the evaluation of recruitment feasibility, scan completion rates, tolerability, missing data rates, USPIO-sensitive MRI metrics, and preliminary effect sizes for imaging-histology associations. Subgroup analyses by tumor type, VS growth status and glioma transformation status will therefore be interpreted as exploratory, to inform future larger-scale studies.

### Data collection, management, and analysis

2.8.

Multimodal imaging analysis will assess the relationships between USPIO uptake and tumor vascular, microstructural, and inflammatory characteristics. Spatial associations will be examined between ferumoxytol-sensitive imaging markers (T_2_, T_2_*, SWI and SELFI values, QSM derived susceptibility values), ASL and DCE-MRI–derived microvascular parameters (*K*^*trans*^, *Ve, Vp*, blood flow), and diffusion metrics (mean diffusivity and fractional anisotropy) using voxel-wise and region-of-interest–based analyses. Early and delayed post-ferumoxytol imaging will be compared to assess time-dependent USPIO redistribution across vascular and extravascular compartments. In patients undergoing surgical resection, imaging-derived measures of USPIO uptake will be correlated with tissue-based markers of inflammation and microvascular proliferation. Spatially resolved elemental iron maps derived from LA-ICP-MS will be compared with adjacent histological sections to support spatial validation of imaging-defined USPIO uptake and compared with corresponding MRI-derived USPIO-sensitive metrics.

### Statistical analysis

2.9.

Differences between ROI volumes on post-GBCA T_1_-weighted and delayed (24–48 hour) USPIO-enhanced T_1_-weighted images will be evaluated using overlap measures, the Dice similarity coefficient (DSC) and Jaccard similarity coefficients (JSC), and the Structural Similarity Index Measure (SSIM) [43,44].

To satisfy primary endpoints, the associations between imaging-derived and tissue-derived parameters will be assessed using Pearson’s product-moment correlation coefficient for approximately normally distributed variables, or Spearman’s rank correlation coefficient for non-parametric or non-linear associations. Secondary analyses will assess temporal changes in imaging metrics, spatial overlap between GBCA and delayed ferumoxytol signal, and associations between USPIO-sensitive metrics and DCE-MRI, ASL and DTI-derived parameters. Comparisons between tumor subgroups, including glioma subtype and VS growth status, will be performed using t-tests or ANOVA where assumptions are met, or suitable non-parametric alternatives where appropriate [14]. These subgroup analyses will be exploratory and interpreted as hypothesis-generating.

Temporal changes in voxel-wise and whole tumor ROI imaging metrics (T_2_, T_2_*, R_1_, QSM-derived susceptibility values) within each tumor voxel will be evaluated using a repeated-measures ANOVA with Greenhouse–Geisser correction for non-sphericity and repeated-measures mixed-effect modeling [45]. Mixed-effects modeling will be preferred where repeated-measures datasets are incomplete. To address multiplicity, analyses will be pre-specified by endpoint hierarchy. For ROI-based secondary analyses involving multiple imaging metrics, false discovery rate correction or Holm–Bonferroni correction will be applied as appropriate. Voxel-wise analyses will be treated as exploratory and will use spatially appropriate correction methods, such as cluster-level correction or false discovery rate correction, where feasible. Findings from these exploratory analyses will be interpreted as hypothesis-generating, rather than confirmatory.

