Our specific hypotheses include that: (1) early (<2 hours) USPIO-enhanced imaging will principally reflect vascular distribution and will correspond with other MRI-derived measures of tumor vascular density and perfusion; (2) delayed (24–48 hours) USPIO-enhanced imaging will principally reflect intracellular USPIO distribution within TAM, and will co-localize with but also extend beyond imaging (GBCA enhancement) and tissue markers of endothelial disruption; (3) that QSM-derived susceptibility estimates and T2*-based measures will provide optimal quantitative reliable measures of TAM density, iron abundance and cellular iron localization with imaged tumors; (4) susceptibility based measures of delayed USPIO uptake (e.g., QSM, R2* mapping) will be greater in growing VS, relative to non-growing tumors, and will reflect an increased abundance of TAM in these tumors; and (5) that regions of higher grade transformation within imaged glioma will show changes on delayed USPIO-enhanced acquisitions, in particular susceptibility-based measures such as QSM, and these regions will show greater TAM abundance on matched tissue sections compared to non-enhancing tumor regions.

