#### Post-scan processing

2.5.1.

Post-contrast T_1_-weighted images acquired following both gadolinium-based contrast agent administration and delayed ferumoxytol imaging (24–48 hours post-injection) will be used to delineate tumor regions of interest (ROI). Tumor segmentation will be performed using semi-automatic approaches in ITK-SNAP [32,33]. Diffusion tensor imaging (DTI) data will be processed to derive fractional anisotropy (FA) and mean diffusivity (MD) maps following eddy-current and motion correction. Multi-delay arterial spin labeling (ASL) will be used to generate quantitative cerebral blood flow (CBF) maps. Amide proton transfer (APT) imaging will be processed to obtain magnetization transfer ratio asymmetry maps. Susceptibility-weighted imaging (SWI), DCE-MRI, and additional quantitative MRI modalities will be processed using established pipelines as described below.

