Dual-injection dual-temporal-resolution DCE-MRI data will be analyzed using the LEGATOS method [34] to derive high-spatial-resolution maps of the following key microvascular parameters: volume transfer constant (*K*^*trans*^), plasma volume fraction (_*Vp*_) and extravascular extracellular volume fraction (_*Ve*_). SWI data acquired at each timepoint will be analyzed using the ‘Segregation and Extravascular Localization of Ferumoxytol Imaging’ (SELFI) formula, which aims to characterize USPIO nanoparticle intra/extravascular compartmentalization [27]. SWI magnitude images acquired at pre-contrast, early post-ferumoxytol, and delayed post-ferumoxytol time points will be co-registered to non-contrast-enhanced T_1_-weighted images. Voxel-wise logarithmic signal intensity ratios will be calculated between pre-contrast and ‘early’ SWI maps or delayed post-contrast images to estimate relative USPIO concentrations. Subtraction of delayed from early ratio maps will yield positive SELFI^+^ and negative SELFI^–^ values. SELFI^+^ values are thought to reflect extravascular USPIO uptake localized to phagocytic cells (TAMs), whereas SELFI^–^ values indicate persistent intravascular USPIO signal, consistent with regions of higher microvascular density [27]. SELFI values will be compared with maps of quantitative relaxometry values (T_2_*, T_2_) generated using existing pipelines and QSM-derived susceptibility maps. As the SELFI method is an investigational approach and not yet an established clinical biomarker, it may be influenced by image registration error, susceptibility artifact, baseline hemorrhage or calcification, residual intravascular USPIO, and nonlinear signal behavior on SWI magnitude images. SELFI maps will therefore be interpreted alongside QSM, T_2_*, SWI and tissue-based measures rather than as a stand-alone marker of cellular USPIO uptake.

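### Dice and Jaccard are the stated measure of GBCA–USPIO volume differences, but outlining and registration error alone lowers them and they carry no direction, so by themselves they cannot show extension beyond GBCA enhancement

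*Protocol article*

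**What the plan says.** Section 2.9 (Statistical analysis) opens with the comparison in question. Its object is given as "Differences between ROI volumes on post-GBCA T_1_-weighted and delayed (24–48 hour) USPIO-enhanced T_1_-weighted images". For the method, the section names two coefficients, saying that these differences "will be evaluated using overlap measures, the Dice similarity coefficient (DSC) and Jaccard similarity coefficients (JSC", and it adds SSIM as a third measure. Later in that section the comparison is listed among the secondary analyses in neutral terms, as "spatial overlap between GBCA and delayed ferumoxytol signal".

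Section 2.5.1 (Post-scan processing) says how the outlines are made: "Tumor segmentation will be performed using semi-automatic approaches in ITK-SNAP".

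Section 1.2 (Objectives) holds the hypothesis on which the comparison bears. Delayed USPIO signal "will co-localize with but also extend beyond imaging (GBCA enhancement) and tissue markers of endothelial disruption". That is a directional statement.

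Section 2.5.1 acknowledges registration error for the SELFI maps ("it may be influenced by image registration error"), and section 2.4 acknowledges spatial uncertainty for matching imaging to histology. No such remark accompanies the outline comparison.

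**The concern.** The plan asks overlap coefficients to do the work of a difference measure. There are two problems.

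- **No natural zero.** A Dice of 1 means perfect agreement, but two outlines of the same unchanged tumor do not reach it. Error can only push the coefficient down, so averaging over patients does not remove the shortfall. A value below 1 is what the second hypothesis predicts, and it is also what outlining and registration error produce.
- **No direction.** Dice and Jaccard are unchanged if the two outlines are swapped. They cannot distinguish USPIO extending beyond GBCA from GBCA extending beyond USPIO. Jaccard adds nothing to Dice, since J = D/(2 − D).

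At stake is the reading of one secondary result. Moderate overlap could be taken as support for signal beyond gadolinium enhancement and carried into the larger studies that this pilot is meant to inform.

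**Working it through.** The article states no Dice value, threshold, tumor size or outlining error, so there is no figure to reproduce. The check asks what Dice to expect when the true extent is the same on both images. Spherical shape, radius and error size are assumptions.

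**Step 1: error only, no true difference**

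- Boundary offset e (one outline uniformly larger): Dice = 2R³ / (R³ + (R + e)³).
- Registration shift d of two equal spheres: Dice = (4R + d)(2R − d)² / (16R³).

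| Radius | Offset 1 mm | Offset 0.5 mm | Shift 1 mm |
|---|---|---|---|
| 5 mm | 250/341 = 0.73 | 250/291.375 = 0.86 | 1701/2000 = 0.85 |
| 10 mm | 2000/2331 = 0.86 | 2000/2157.625 = 0.93 | 14801/16000 = 0.93 |
| 15 mm | 6750/7471 = 0.90 | 6750/7098.875 = 0.95 | 51301/54000 = 0.95 |

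Between 5 and 15 mm radius, the same 1 mm error moves Dice by 0.17 (offset) or 0.10 (shift).

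A small simulation (10 pairs per setting) drew two independent outlines of one sphere, each with smooth random boundary error of SD 1 mm. Mean Dice was 0.60, 0.83, 0.88 and 0.92 at radius 5, 10, 15 and 20 mm. These values are lower than the closed-form ones because both outlines carry error.

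**Step 2: true difference, no error**

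If the USPIO outline contains the GBCA outline and is larger in volume by a fraction x, Dice = 2/(2 + x).

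- x = 0.2: 2/2.2 = 0.909
- x = 0.3: 2/2.3 = 0.870

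Both lie inside the 0.86–0.93 that 1 mm of error alone gives at 10 mm radius. If instead the GBCA outline were the one 20% larger, Dice would again be 0.909.

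**Step 3: would other measures from the same outlines do better?**

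Take a GBCA outline of radius 10 mm:

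| Measure | True 20% extension | 1 mm shift only | 1 mm one-sided offset only |
|---|---|---|---|
| Dice | 0.909 | 0.925 | 0.858 |
| Signed volume difference | +20% | 0% | (1331 − 1000)/1000 = +33% |
| Fraction of USPIO outline outside GBCA outline | 0.2/1.2 = 0.17 | 1 − 0.925 = 0.075 | 331/1331 = 0.25 |

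The signed volume difference shows direction and ignores a pure shift. Random outlining error also tends to cancel in it. In the simulation with 1 mm SD, mean volume ratios were 0.98 to 1.04 for radii of 7.5 to 20 mm, while mean Dice was 0.78 to 0.92. At 5 mm radius the ratio was unstable (1.40). The signed difference does not remove outlining error, as the last column shows, so a reader reference is still needed. The outside fraction cannot fall below zero, so random error tends to raise it, and it needs the reference too.

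**The case against.** **The article is a condensed document.** Repeat outlining and reader reliability are commonly left to a full protocol, imaging manual or SAP, none of which is shown. A reader might infer that no reliability step is planned. The article does not support that inference, and the point does not rest on it. It rests on the measure that the article does fix.

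**Nothing is decided on Dice.** No test, threshold or p-value is attached to it, the analysis is secondary, and the same section also calls it spatial overlap. All of this stands and limits the weight of the point. It does not change what the coefficients can show. SSIM, the third measure named, is an image-similarity index and supplies neither a volume difference nor its direction.

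**Other data bear on the hypothesis.** Section 2.3.1 gives priority to susceptibility and T2/T2* measures for delayed assessment, and section 1.2 lists the volume of USPIO signal among the secondary endpoints. So the T1-weighted outline comparison is not the only evidence, and the volumes needed for a signed difference should already exist. That makes the change easy; it does not make it unnecessary.

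**Comparisons by tumor type or size.** A reader might infer that Dice will be compared between glioma and VS, or between large and small VS, and will mostly reflect size. The article states no such comparison. Its subgroup sentence does not name Dice and is declared exploratory. Size dependence matters only if such a comparison is made.

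**The size of the effect is assumed.** This is correct. The 0.73 at 5 mm radius comes from a one-sided offset that makes one outline 73% larger (216/125), which is a harsh case. For diameters of 40–50 mm with 0.5 mm error, Dice stays at about 0.96 or above.

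**A repeat outline does not capture registration error.** This is also correct. Dice minus repeat Dice would still lean toward discordance, so that contrast alone is not enough.

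**Conclusion.** The point holds in a limited form. As written, the comparison cannot by itself separate outlining and registration error from a true GBCA–USPIO difference, and it cannot show which agent marks the larger region. Under the assumption of spherical tumors and 1 mm of error, the two closed-form models put Dice with no true difference at about 0.73–0.85 at 5 mm radius, 0.86–0.93 at 10 mm and 0.90–0.95 at 15 mm. The direction of the effect (lower overlap in smaller tumors) was the same under all three error models. Its size depends on tumor sizes and reader error, which the article does not give, and it is small for large tumors that are outlined well.

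The primary endpoint, the association between imaging and tissue, does not use Dice or Jaccard. No error rate is affected. The gain is a secondary result that can be interpreted.

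**What to change.** In section 2.9 or the SAP:

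1. Keep Dice as a descriptive measure of overlap. Jaccard can be dropped or kept as a restatement of Dice.
2. Add the signed volume difference (USPIO minus GBCA) and the fraction of the USPIO outline outside the GBCA outline. Both come from the outlines already planned.
3. Have the existing reader outline the post-GBCA scan a second time, without sight of the first outline, in all patients or a random half ("The planned number of participants is 39 (12 sporadic VS, 12 NF2-VS patients, 15 glioma patients", so 39 or about 20 repeats). Compute the same three measures between the two GBCA outlines and read the GBCA–USPIO values against them.
4. State that this repeat reflects reader error only. Registration error remains in Dice and in the outside fraction but, as a pure shift, does not affect the signed volume difference. A systematic difference in how the edge appears under the two contrast agents would not be captured by the repeat either.
5. If overlap is ever compared between groups with different tumor sizes, also report a surface distance in mm (a uniform 1 mm offset is 1 mm at any radius) or account for tumor volume.

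The cost is some hours of the existing reader's time and a few sentences of text. No new scans or staff are needed.

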### Objectives

1.2.

In this pilot study, we investigate the candidate USPIO agent ferumoxytol as a noninvasive imaging marker of TAM-driven inflammation in suspected transforming LGGs and VS. We hypothesize that delayed ferumoxytol-sensitive MRI signals reflect the transition from vascular circulation to extravascular and TAM-associated USPIO uptake within the tumor microenvironment.

The primary endpoint is to assess the association between delayed ferumoxytol-induced MRI susceptibility changes and histologically quantified TAM density, across CNS tumor subtypes with differing vascular and microenvironmental characteristics. Within this, the specific secondary endpoints are to:
Characterize the volume, pattern, and intensity of early and delayed USPIO-enhanced MRI signal in gliomas and VS and define the optimal qualitative (e.g., susceptibility-weighted imaging, SWI) and quantitative methods (e.g., quantitative susceptibility mapping, QSM and T2* mapping) for assessing delayed USPIO cellular internalization.Examine the relationship between GBCA enhancement patterns and the extent, spatial distribution and signal intensity of early (<2 hours) and delayed (24–48 hours) USPIO uptake in both glioma and VS cohorts.Examine the association between delayed USPIO-enhanced MRI signal, tissue markers of TAM abundance and VS clinical behavior, such as size and VS growth status.Evaluate QSM-derived susceptibility values as a quantitative imaging marker for detecting USPIO cellular internalization in CNS tumors, and the relationship with tissue measures of iron abundance and localization.Assess differences in USPIO-related signal changes and immune cell density between histologically confirmed transformed and non-transformed glioma regionsEvaluate the phenotype and spatial distribution of TAMs in each tumor and their relationship to USPIO uptake

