### Tissue collection

2.4.

Written informed consent is obtained from all participants for the collection and analysis of tumor tissue, with both formalin-fixed paraffin-embedded (FFPE) and fresh-frozen specimens collected at surgery. Immunohistochemistry and immunofluorescence analyses are performed on FFPE and fresh-frozen tissue to characterize USPIO uptake across immune and nonimmune cell populations. For extra-axial tumors such as VS, tumors are often completely resected allowing comparison of ferumoxytol imaging datasets with tissue across the entire tumor volume. For intra-axial tumors such as glioma, image-guided tissue sampling of non-enhancing and enhancing regions on delayed phase (>24 hours) post ferumoxytol imaging can be performed using neuronavigation software.

The interval between the final ferumoxytol MRI scan and tissue acquisition will be recorded. Surgery will be scheduled as close as clinically feasible to the final imaging timepoint, determined by clinical urgency, theater availability and standard care pathways. In line with the usual clinical pathway at our institution, for participants with glioma, it is expected, that surgery will be performed within 24 hours of the final MRI scan. For participants with VS, it is expected that surgery will be performed within 4 weeks of the final MRI scan. Acquired imaging from each timepoint (post GBCA and post ferumoxytol) will be fused using neuronavigation software. For participants with glioma, sampling will target regions within the tumor, where safe and appropriate to do so, corresponding to delayed ferumoxytol related changes, contrast enhancement and non-enhancing tumor. For participants with VS, complete or near-complete resection is standard practice at our institution but we will also use neuronavigation to allow for tissue sampling of different regions within the tumor. Sample location will be recorded for later comparison with MRI-derived maps. Imaging–histology registration will be interpreted with recognition of unavoidable spatial uncertainty arising from brain shift, tissue deformation, sampling limitations, fixation and sectioning effects, and differences between *in vivo* MRI resolution and *ex vivo* histological resolution.

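### The primary imaging–TAM correlation has no patient or tumor-type term, although several samples per tumor are planned and the endpoint spans unlike tumor types

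*Protocol article*

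**What the plan says.** Section 1.2 (Objectives) makes the primary endpoint the association between delayed ferumoxytol-induced susceptibility change and "histologically quantified TAM density, across CNS tumor subtypes with differing vascular and microenvironmental characteristics".

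Section 2.9 (Statistical analysis) gives the method for it: "the associations between imaging-derived and tissue-derived parameters will be assessed using Pearson’s product-moment correlation coefficient" when variables are roughly normal, "or Spearman’s rank correlation coefficient for non-parametric or non-linear associations". No other term enters. Mixed-effects models appear in the same section only for change in imaging metrics over time.

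Section 2.4 (Tissue collection) describes where tissue comes from. In glioma, "sampling will target regions within the tumor", subject to safety, and the targets are regions "corresponding to delayed ferumoxytol related changes, contrast enhancement and non-enhancing tumor". In VS, "we will also use neuronavigation to allow for tissue sampling of different regions within the tumor". Sample locations are recorded so that they can be compared with the MRI maps.

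Section 2.7 plans 39 participants (12 sporadic VS, 12 NF2-VS, 15 glioma) on feasibility grounds. It treats analyses by tumor type as exploratory and lists preliminary imaging–histology effect sizes among the outputs.

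**The concern.** A Pearson or Spearman test takes its pairs to be independent draws from one population. The design described can break this in two ways.

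1. **Clustering.** Samples from one tumor share that patient's general signal level and TAM level. If each sample counts as a separate pair, the nominal sample size overstates the information.
2. **Tumor type.** The article places VS outside the blood–brain barrier (section 1.1.2), calls glioma and VS biologically distinct (section 2.7), and expects surgery within 24 hours of the last scan in glioma but within 4 weeks in VS (section 2.4). Average signal and average TAM density may therefore both differ by type. A pooled correlation then mixes the gap between types with the question of interest: whether signal tracks TAMs within a type or within a tumor.

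The pilot's imaging–histology effect size is meant to inform larger studies, so bias in r matters even if nobody acts on a p-value.

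**Working it through.** **Plan's own figure.** 12 + 12 + 15 = 39, which agrees. The article gives no alpha, power or target correlation, so there is no power calculation to reproduce.

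**Assumptions, because the article gives no values.** Tissue from 27 patients (15 glioma, 12 VS); 3 samples per glioma and 2 per VS where clustering is examined; the same ICC for imaging and TAM density; a tumor-type mean gap of d within-type SDs in both variables; nominal two-sided 5% test; true within-type correlation zero unless stated.

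**1. Clustering alone (d = 0).** There are 15×3 + 12×2 = 69 samples. The size-weighted mean cluster size is (15×9 + 12×4)/69 = 183/69 = 2.65. The variance of r under the null is inflated by about D = 1 + (2.65 − 1) × ICC². The false-positive rate is then about 2 × [1 − Φ(1.96/√D)].

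| ICC | D | √D | Approximate rate | Simulated rate |
|---|---|---|---|---|
| 0.3 | 1.15 | 1.07 | 6.7% | 6.5–6.7% |
| 0.5 | 1.41 | 1.19 | 9.9% | 9.7–10% |
| 0.7 | 1.81 | 1.35 | 14.5% | 14–15% |

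Simulated rates are the range over separate runs of 8,000 to 20,000 replicates. Mean r was 0.00 throughout. False positives split evenly by sign (at ICC 0.5, about 4.9% positive and 4.9% negative). With 3 samples from every patient the rates were 7.0%, 11.1% and 16.9%. At ICC 0 there was no inflation.

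**2. Pooling alone (one value per patient).** With glioma share q = 15/27, q(1 − q) = 180/729 = 0.247. Put v = 0.247 × d². For a within-type correlation ρ, the pooled correlation is (ρ + v)/(1 + v) if both means differ in the same direction, and (ρ − v)/(1 + v) if they differ in opposite directions.

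| d (SD) | v | Pooled r at ρ = 0, same direction | Opposite direction | Simulated rejection rate |
|---|---|---|---|---|
| 0.5 | 0.062 | 0.06 | −0.06 | about 6% |
| 1.0 | 0.247 | 0.20 | −0.20 | 17% |
| 1.5 | 0.556 | 0.36 | −0.36 | 48% |

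If all 39 patients gave tissue (24 VS), r at 1 and 1.5 SD would be 0.19 and 0.35.

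A real association can also be hidden. With an assumed ρ = 0.3 and opposite gaps of 1 SD, pooled r is (0.3 − 0.247)/1.247 = 0.04. At 1.5 SD it is (0.3 − 0.556)/1.556 = −0.16.

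**3. Does averaging to one value per patient cure it?** Only the clustering part. With 3 samples per patient averaged, ICC 0.5 and a same-direction 1 SD gap, the unadjusted correlation of patient means still rejected in 29.6% of runs.

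**4. Does the remedy work?** In the scenarios run, a within-patient correlation (where there were several samples per patient) and a correlation of patient means adjusted for tumor type both rejected in 4.7% to 5.4% of runs.

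**The case against.** **Both premises are inferred.** Section 2.9 states neither a unit of analysis nor that types are pooled. Glioma sampling is conditional on safety, and whole-tumor comparison in VS would suit one value per tumor. The endpoint's wording, "across CNS tumor subtypes with differing vascular and microenvironmental characteristics", could mean assessed within each subtype. An article also leaves much to a full protocol or SAP. This stands as a limit on certainty, so the consequences above are stated as conditional. It does not remove the point: the article does fix the primary method, region-targeted sampling with recorded locations points to sample-level pairs, and making by-type analyses exploratory points to a pooled primary analysis.

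**The sizes are assumed.** This also stands. The ICC and the gap have no basis in the article, a 0.5 SD gap does little, and fewer VS patients may yield tissue, since static tumors may go to surveillance.

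**Two stronger readings are tempting.**
- A reader might infer that both problems push toward a positive finding. They do not: clustering leaves r centered on zero and adds errors in both directions, and pooling raises r only if both means differ the same way. The article does not give the direction.
- A reader might infer that unpaired t-tests or ANOVA are assigned to transformed versus non-transformed regions of the same glioma. Section 2.9 names those tests for tumor subgroups such as glioma subtype and VS growth status. It names no test expressly for the region comparison, and paired tests are not excluded.

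**Conclusion.** The point holds in conditional form: the primary method as written does not fit the data structure the article describes. Clustering, if samples are the unit, is a modest problem of precision at the assumed sample counts and ICCs. Pooling, if glioma and VS are combined without adjustment, is the more serious problem because it distorts the estimate itself; it remains with one value per patient and becomes material from a gap of about 1 SD. Rejection rates here only gauge the distortion, since the study states no decision threshold. As a feasibility-sized pilot whose analysis can be changed without new data, this is a should-fix.

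**What to change.** - State the unit of analysis for the primary endpoint.
- If there are several samples per patient, make the primary analysis a sample-level linear mixed model of TAM density (transformed if needed) on delayed susceptibility change, with tumor type as a fixed effect and a patient random intercept. Split the imaging variable into the patient mean and the deviation from it, so that within-patient and between-patient associations are estimated separately.
- If there is one value per patient, use a correlation adjusted for tumor type.
- Report the estimates with 95% CIs separately for glioma and VS.
- Keep the raw pooled correlation as description only, and do not carry it forward as the effect size for a later study.

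The cost is revised wording in section 2.9 and modest extra analysis. Intervals will be wider, and those for each tumor type wider still. No new data are needed.

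### Glioma tissue sites are chosen partly by ferumoxytol signal, so the primary correlation depends on the site mix; report a slope beside it

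*Protocol article*

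**What the plan says.** All references are to the protocol article.

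- **Primary endpoint (1.2 Objectives):** to "assess the association between delayed ferumoxytol-induced MRI susceptibility changes and histologically quantified TAM density", across tumor subtypes.
- **Primary statistic (2.9 Statistical analysis):** "associations between imaging-derived and tissue-derived parameters will be assessed using" Pearson's "product-moment correlation coefficient for approximately normally distributed variables", or Spearman's rank coefficient otherwise. No slope is named for this endpoint; mixed-effects models appear only for changes over time.
- **Glioma tissue (2.4 Tissue collection):** the section first describes "image-guided tissue sampling of non-enhancing and enhancing regions on delayed phase (>24 hours) post ferumoxytol imaging" as something that can be done. It then says that sampling will target regions "corresponding to delayed ferumoxytol related changes, contrast enhancement and non-enhancing tumor", as far as is safe.
- **VS tissue (2.4):** "tumors are often completely resected allowing comparison of ferumoxytol imaging datasets with tissue across the entire tumor volume". Navigated sampling of different tumor regions is also planned, with no stated rule on signal.
- **Use of the result (2.7 Sample size and tumor groups):** the pilot is to yield "preliminary effect sizes for imaging-histology associations". Subgroup analyses by tumor type, growth and transformation status are exploratory, "to inform future larger-scale studies".
- **Stated limitation (2.4):** spatial uncertainty between imaging and histology. Selection of sites on signal is not mentioned.

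**The concern.** The delayed ferumoxytol signal is both the explanatory variable of the primary endpoint and one of the criteria for choosing where glioma tissue is taken. A correlation coefficient is not a property of the biology alone. It rises when the sampled values of the explanatory variable are more spread out than in the tumor as a whole, and falls when they are less so. A correctly specified regression slope is not biased by selection on the explanatory variable.

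If the glioma r is used as a planning effect size for a study that samples differently, that study may be too small. If it is set beside a VS r from whole-tumor tissue, part of any difference may come from how tissue was sampled. The article also wants a quantitative marker of macrophage density, which calls for a slope and residual SD; r supplies neither.

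**Working it through.** The article gives no expected correlation, alpha, power or site mix. Its only figure here is the planned number, 12 + 12 + 15 = 39, set by feasibility, so there is no power calculation to reproduce. Everything below rests on assumptions: a linear relation, bivariate normal values, and a true whole-tumor correlation ρ of 0.40 unless stated.

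**Step 1. Effect of spread on r.** Let u be the SD of signal at the sampled sites divided by its SD over the whole tumor. Then

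r = ρu / √(1 + ρ²(u² − 1)).

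For equal numbers of sites from the upper and lower share q, u² = 1 + c·φ(c)/q, where c is the normal cut-off for q. With q = 0.20: c = 0.842, φ(c) = 0.280, u² = 2.18, u = 1.47, and r = 0.588 / √1.186 = 0.54.

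| Sites obtained (ρ = 0.40) | u | r |
|---|---|---|
| Upper and lower halves equally | 1.00 | 0.40 |
| One from top third, one from the rest | 1.02 | 0.41 |
| One from top fifth, one from the rest | 1.08 | 0.43 |
| One from top tenth, one from the rest | 1.18 | 0.46 |
| Outer thirds, one third of sites unselected | 1.15 | 0.45 |
| Outer fifths, one third unselected | 1.34 | 0.50 |
| Outer tenths, one third unselected | 1.58 | 0.57 |
| Outer thirds only | 1.22 | 0.47 |
| Outer fifths only | 1.47 | 0.54 |
| Outer tenths only | 1.80 | 0.62 |
| Top third only | 0.53 | 0.23 |
| Top fifth only | 0.47 | 0.20 |

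In simulation the slope stayed at 0.40 under every mixed scheme. Spearman behaves alike: for outer fifths with one third unselected it moves from about 0.385 to 0.498. Under that same mix, ρ of 0.2, 0.3, 0.4, 0.5 and 0.6 gives r of 0.26, 0.39, 0.50, 0.61 and 0.71.

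**Step 2. Effect on planning.** With a two-sided 5% test and 80% power, N = ((1.960 + 0.842) / atanh r)² + 3. For r = 0.40, N = (2.802 / 0.4236)² + 3 = 46.7, so 47. If the true r is 0.40 but planning uses:

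- 0.41: N = 45, real power about 78%
- 0.46: N about 35, about 67%
- 0.504 (outer fifths, one third unselected): N = 29, about 58%
- 0.54: N = 25, about 51%
- 0.618 (outer tenths only): N = 19, about 40%

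**Step 3. Mislocation.** If the paired imaging value has reliability 0.7, randomly placed sites give r = 0.40 × √0.7 = 0.335. Targeted sites (outer thirds or fifths, one third unselected) give 0.38 to 0.43. With reliability 0.5 the values are 0.283 and 0.32 to 0.37.

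**Step 4. Chance error.** Treating 15 gliomas as 15 independent values, r = 0.5 has a 95% CI of tanh(0.549 ± 1.96/√12), that is −0.02 to 0.81.

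**Step 5. Correcting r.** An observed 0.504 with u = 1.34 returns (0.504/1.34) / √(1 + 0.504²(1/1.34² − 1)) = 0.376 / 0.942 = 0.40. The SD must be on the scale of the tissue samples. If a single-voxel SD were used and were 1.4 times the regional SD (an assumption), a slope of 0.40 and residual variance of 0.84 give 0.56 / √(0.3136 + 0.84) = 0.52, which would put the overstatement back.

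**The case against.** The strongest reply is that the direction is not settled. Overstatement requires sampled sites more spread in signal than the tumor. Section 2.4 names three target classes, one of them contrast enhancement, and does not equate non-enhancing tumor with the lowest ferumoxytol signal. The outer-tails-only rows are therefore the extreme end and not the described scheme; pairing a changed site with one from the rest of the tumor moves r only to 0.41 to 0.46. Surgical safety makes the realized mix unknown, and the acknowledged mislocation lowers r. With 15 gliomas, chance error exceeds the bias. The effect sizes are called preliminary, subgroup work is exploratory, and a slope may already be in the full protocol or analysis plan, which are not shown.

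Most of this stands and limits the point. What it does not remove is that the size of r is partly set by the site mix. An offset of unknown size does not make r easier to interpret, and the confidence interval does not show the bias. The slope is protected from selection on signal, though not from mislocation.

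A reader might also infer that VS samples are not chosen by signal. Section 2.4 does not say so: imaging from each timepoint is fused for navigation, and no VS rule is stated either way. Only the contrast with whole-tumor VS tissue has support in the text.

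**Conclusion.** The point holds in a limited form. Glioma sites are selected partly on the explanatory variable of the primary endpoint, the article names only a correlation for that endpoint, and it means to produce effect sizes from it. At an assumed true r of 0.40, the shift runs from about 0 to +0.2 when changed and unchanged sites are contrasted, and reverses if only changed sites are obtained. These figures rest on linearity, normality and assumed site mixes.

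A reader might infer that the whole primary result is inflated and cannot be used later. The documents do not support that. Only the glioma sites are clearly affected (15 of 39 participants, possibly a larger share of those giving tissue, since some VS patients may not have surgery). The glioma r does carry to a study with the same targeted sampling. Selection on signal also does not create an association where none exists. This is an inexpensive improvement to the analysis and does not call the design into question.

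**What to change.** In section 2.9:

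1. Beside r, report the regression slope of macrophage density on the delayed imaging change, with its 95% CI and residual SD. Include a patient effect where a patient gives several sites.
2. State the number of glioma sites obtained in each target class.
3. Label the glioma r as specific to the targeted sites.
4. If r is used for planning or for comparing glioma with VS, range-correct it with the whole-tumor signal SD. Compute that SD on regions of the same size as the tissue samples, not on single voxels, and correct only where a linear relation is reasonable.

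The targeted sampling itself need not change, and the whole-tumor signal comes from MRI already planned. The cost is slightly more analysis, and the planning correlation may become less favorable.
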